## Introduction

Childhood trauma is pervasive, with around 50% of adolescents experiencing at least one potentially traumatic event (PTE) before adulthood [1-3]. Posttraumatic stress disorder (PTSD) is the most common disorder that can develop after experiencing PTE and occurs in around 16% of PTE-exposed adolescents, with a range of 8%-33%. Importantly, the variability within this range is influenced by the type of trauma and gender. In particular, PTSD is less prevalent in boys exposed to noninterpersonal trauma, while girls exposed to interpersonal trauma are at a greater risk of developing PTSD [4]. PTSD manifests through symptoms such as re-experiencing (ie, flashbacks, nightmares, dissociation, repetitive distressing images or sensations, and physical sensations such as pain, sweating, nausea, or trembling), avoidance and emotional numbing, negative alterations in cognitions and mood, and hyperarousal (ie, irritability, angry outbursts, sleep disturbances, and difficulty concentrating) [5].

Furthermore, PTSD significantly affects an individual’s quality of life [6,7]. Adolescents with PTSD have been found to show high rates of psychopathology at the age of 18 years, including 48.8% engaging in self-harm, 20.1% attempting suicide, 54.7% diagnosed with major depressive disorder, 23.8% with generalized anxiety disorder, and 27% with conduct disorder [8]. In addition, subclinical PTSD (sPTSD) in adolescents is often neglected. However, adolescents with sPTSD can experience similar distress as adolescents with full-blown PTSD [9]. These findings emphasize the critical importance of early treatment for both clinical and sPTSD.

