#### Secondary Objectives

The secondary objectives of the study are to investigate whether BITT for adolescents with PTSD:

in comparison to a WLCG, demonstrates effectiveness in reducing comorbid psychiatric symptoms (ie, anxiety, depression, and anger) and improving the quality of life;is safe (ie, does not increase suicide attempts or self-harm)reduces dropout rates;is affected by moderators (ie, age, gender, socioeconomic status [SES], type of trauma, number of traumatic events, comorbidity, caregivers PTSD, and treatment center) in its effect on PTSD symptoms and BITT dropout (moderators: residency [ie, urban and rural area] and ethnicity).

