#### Risk-Behavior and Safety Questionnaire

We will assess risk behaviors by administering a self-report questionnaire based on previous work by Hendriks et al [25], who administered this questionnaire to children aged 12-18 years. This questionnaire assesses suicidal ideation, self-harm, and aggressive behavior with 8 items using an 11-point Likert scale, ranging from “no, not at all” (=0) to “yes, very much” (=10) [25]. Higher scores reflect a higher severity of symptoms. Alcohol use, drug use, inclination to medication, crisis contacts with mental health care professionals, and psychiatric hospitalization will be measured with 7 items on a dichotomous scale (yes or no). The psychometric properties of this instrument have not yet been examined.

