### Statistical Analysis

We will conduct the analyses in consultation with a statistical expert. Data analyses will include the following:

We will define the effects of BITT in terms of group differences between the BITT and WLCG. These differences will be tested according to both the intention-to-treat-principle and completers’ analyses. That is, the pre, post, and follow-up changes (BITT vs WLCG) on the continuous outcomes (ie, trauma symptoms, anxiety symptoms, depression symptoms, anger symptoms, quality of life, and self-harm) will be tested with mixed models; dichotomous outcomes (ie, suicide attempts and dropout) with generalized estimating equation (GEE).Mixed models will also be used to investigate possible moderation effects, which concern effects of (1) age, gender, SES, type of trauma, number of traumatic events, comorbidity, caregivers’ PTSD, and treatment center on PTSD; and (2) residency (ie, urban and rural) and ethnicity on BITT dropout.The qualitative interviews about the experiences of adolescents, caregivers, and therapists with regard to BITT will be verbatim transcribed and analyzed to conform to qualitative research standards.

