### Ethics Approval

This study will be conducted in accordance with the Declaration of Helsinki. The ethics review board of the Amsterdam University Medical Center in the Netherlands approved this study (2022.0347, September 12, 2022). We will handle participant data in compliance with the General Data Protection Regulation (GDPR). All adolescents will give written informed consent, and legal guardians of adolescents aged 12-15 years will also provide consent before conducting any study procedures. All serious adverse events will be monitored and reported to the Medical Ethical Committee of the Amsterdam University Medical Center until the end of the study. In addition, during the measurements (directly, 3, 6, and 9 months after the BITT) we assess PTSD symptoms, comorbid symptoms, and risk behavior. In case of safety concerns, we contact the referring professional of the adolescent. Participants will receive a voucher of 10 euros (US $11.36) upon completing the final measurement.

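### Self-harm is half of the safety question, but its only stated test compares mean change between arms, which can net a benefit in existing self-harmers against new or worsening self-harm in others

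*Protocol article*

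**What the plan says.** Under Secondary Objectives, one question is whether BITT "is safe (ie, does not increase suicide attempts or self-harm". Self-harm is therefore one of two named components of safety.

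The Risk-Behavior and Safety Questionnaire supplies the measure: "This questionnaire assesses suicidal ideation, self-harm, and aggressive behavior with 8 items using an 11-point Likert scale". The article does not say how many of the 8 items concern self-harm, how they are worded or how they are scored. A separate block covers alcohol, drugs, medication, "crisis contacts with mental health care professionals, and psychiatric hospitalization will be measured with 7 items on a dichotomous scale (yes or no". Self-harm is not in that yes/no block. Table 2 shows the questionnaire given to adolescents at T0 to T4.

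Statistical Analysis assigns the methods. Between-arm differences in change on the continuous outcomes, with self-harm on that list, go to mixed models ("depression symptoms, anger symptoms, quality of life, and self-harm) will be tested with mixed models"). The yes/no list is short: "dichotomous outcomes (ie, suicide attempts and dropout) with generalized estimating equation (GEE". The moderator analyses concern PTSD and BITT dropout, not self-harm.

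Under Ethics Approval, "All serious adverse events will be monitored and reported to the Medical Ethical Committee", and safety concerns are passed to the referring professional.

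**The concern.** Whether a treatment increases self-harm is a question about people: how many start, and how many get worse. A difference in mean change answers another question, namely whether the average score moved more in one arm. The two answers can diverge when some participants have room to fall and others start at or near zero and can only rise.

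The Introduction suggests such a mix, describing adolescents with PTSD as "including 48.8% engaging in self-harm" at age 18. The Discussion expects BITT to change symptoms while the waitlist arm stays unchanged. If that hypothesis carries over to self-harm, existing self-harmers would improve in the BITT arm only, which is the condition under which masking can occur.

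At stake is the safety statement in the final report. A finding of no increase in mean self-harm could be read as reassurance for adolescents who began to self-harm after BITT, with no stated comparison to contradict it.

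**Working it through.** The plan gives no figure for self-harm, so there is none to reproduce. The sample size calculation does not bear on this point.

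**Inputs from the article.** 50 per arm (Study Design). Prevalence of self-harm 48.8% (Introduction), a background figure used here as an assumption: 0.488 × 50 ≈ 24 self-harmers and 26 others per arm. Items run 0-10.

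**Inputs that are assumptions.** The 26 others score 0 at baseline. Onset is at 5 points, in 6/26 with BITT and 1/26 with waitlist. Self-harmers have baseline mean 5 and SD 2, and SD of change 2. The fall among them is varied.

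**Step 1: the between-arm contrast by arithmetic** (ignoring the floor at 0).

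Difference in mean change = onset part − differential-fall part.

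- Onset part: 5 × (6 − 1)/50 = +0.50 points, in the direction of harm.
- Falls of 2 v 0.5: (2 − 0.5) × 24/50 = 0.72; net 0.50 − 0.72 = −0.22, apparently favouring BITT.
- Falls of 1 v 0.5: 0.5 × 24/50 = 0.24; net +0.26.
- Equal falls: net +0.50.
- Break-even differential fall: 0.50 × 50/24 ≈ 1.04 points.

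Only the difference in falls enters. Whatever is common to both arms, regression to the mean included, drops out.

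**Step 2: simulation of a baseline-adjusted mean comparison on the same inputs.**

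| Fall among existing self-harmers, BITT v waitlist | Estimate favours BITT | Significant increase found |
|---|---|---|
| 2 v 0.5 | about 64% | about 0.6% |
| 1.5 v 0.5 | about 42% | about 3% |
| 1 v 0.5 | about 21% | about 11% |
| equal | about 7% | about 27% |

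New onset averages 6 versus 1 in every row.

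**Step 3: how many extra cases a differential fall cancels.** With prevalence p, differential fall Δ and onset height m, the extra new cases per 50 that bring the mean difference to zero are 50 × p × Δ / m.

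- p = 0.488, Δ = 1, m = 5: 50 × 0.488 × 1/5 ≈ 4.9.
- p = 0.488, Δ = 2, m = 5: ≈ 9.8.
- p = 0.488, Δ = 1, m = 3: ≈ 8.1.
- Over p from 30% to 60%, Δ from 1 to 2 and m from 3 to 5: 3 to 20 (the 20, at p = 60%, is every adolescent not self-harming at baseline).

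In simulations at break-even (baseline scores 3-9 among self-harmers, 5% background onset), the mean test rejects in about 5% of runs, its chance level. With m = 5, the proportion rising by 3 or more points is then about 13% v 4% for Δ = 1 and 22% v 4% for Δ = 2.

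**Step 4: what a count of worseners could show.** In those two scenarios a Fisher test on the proportion is significant in about 19% and 66% of runs at 50 per arm, and about 10% and 51% at 37 per arm (50 × 0.75 = 37.5 after the planned 25% dropout). For 6/26 v 1/26 itself, Fisher p = 0.10, and the test is significant in about 36-39% of runs.

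**The case against.** - **A reader might infer that the planned test will hide harm, or will report a benefit.** The documents do not support that. It takes a fall among existing self-harmers that is larger under BITT than under waitlist, and nothing in the article gives its size. The waitlist arm may receive other care, including EMDR and TF-CBT, so the difference could be small. With equal falls the estimate points towards harm in about 93% of runs. This stands, and is why a range is shown.
- **A reader might blame regression to the mean, or compute the change within the BITT arm:** −2 × 24/50 + 5 × 6/50 = −0.36. Neither describes the planned test. Regression to the mean is common to randomised arms, and the plan compares arms. If waitlist self-harmers also fell by 2 points, the contrast would be +0.50.
- **The 48.8% is borrowed.** It describes age 18 with PTSD; the trial enrols ages 12-18 and admits subthreshold PTSD. How many will score 0 is unknown. This stands.
- **Safety does not rest on this mean alone.** Suicide attempts are tested as a yes/no outcome, crisis contacts and hospitalisation are recorded, and serious adverse events are reported. Serious individual cases would surface. But no between-arm comparison of them is stated for self-harm, and events that are not serious would go uncompared.
- **A count of worseners could be left to an analysis plan that is not shown.** In part. The article does, however, fix the treatment of self-harm as continuous and names only two dichotomous outcomes, so this is a stated choice rather than an omitted detail.
- **The added analysis has little power.** True; it should be read as an estimate.

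**Conclusion.** The concern holds as a mismatch between question and test. Safety asks whether self-harm increases; the only stated test of self-harm is a between-arm difference in mean change, which nets improvement against harm. Masking is possible, not demonstrated, and needs a differential benefit among those already self-harming. Under the assumed onset of 6/26 v 1/26, the chance that the estimate favours BITT runs from about 7% with equal falls to about 64% with falls of 2 v 0.5, and the chance of a significant increase from about 27% down to about 0.6%. Even with no differential benefit, the mean test usually misses this onset. All inputs other than the arm size and the borrowed 48.8% are assumptions. This is a cheap improvement to the plan, not a fatal flaw.

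**What to change.** Keep the mixed model for self-harm and place beside it, at T1 and at T2, the proportion in each arm with new or worsened self-harm since T0. Both visits precede the waitlist arm's BITT, so the randomised comparison is intact. Define new or worsened by a minimum rise in score, fixed before any unblinded analysis; any score above 0 is too loose, since a rating of 1 out of 10 would count as onset. State which items form the self-harm score. Report the risk difference with its 95% CI, and do the same for the suicidal-ideation items.

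The cost is a few lines of analysis text and agreement on the threshold; the data are already collected at T0, T1 and T2. The downside is imprecision: at 50 per arm, power for 5% v 15% is about 38% and for 5% v 25% about 81%. The text should therefore say that a non-significant difference, in either analysis, will not be read as proof of safety.

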### Study Design

In this multicenter, single-blinded RCT, we will examine the effectiveness of BITT compared to a WLCG. Participants will be recruited over 27 months (October 2022-December 2024). To determine the effectiveness of BITT, we will compare the outcomes of the BITT intervention group (n=50) with the outcomes of a WLCG (n=50). We will conduct assessments at similar time points for both groups: at baseline (T0), directly after BITT or WLCG (T1), and at 3 (T2), 6 (T3), and 9 (T4) months follow-up after the baseline measurement. The WLCG will receive BITT after the 3-month follow-up assessment. Figure 1 provides an overview of the study design.

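### A GEE test of group differences in suicide attempts cannot support the no-increase safety objective at about 50 per arm, and the article does not name the source of the attempt data

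*Protocol article*

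**What the plan says.** In the Protocol article, Secondary Objectives asks whether BITT "is safe (ie, does not increase suicide attempts or self-harm". Suicide attempts are therefore one of the two named components of safety.

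Statistical Analysis sets the form of inference: "We will define the effects of BITT in terms of group differences between the BITT and WLCG". These differences are to be tested, with mixed models for continuous outcomes (self-harm among them), and "dichotomous outcomes (ie, suicide attempts and dropout) with generalized estimating equation (GEE". The article states no margin or acceptable upper bound for an increase in attempts.

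The only adolescent safety instrument in Table 2 is the risk-behaviour questionnaire. Of its scaled part the article says: "This questionnaire assesses suicidal ideation, self-harm, and aggressive behavior with 8 items using an 11-point Likert scale". The yes/no part covers alcohol, drugs, medication, and "crisis contacts with mental health care professionals, and psychiatric hospitalization will be measured with 7 items on a dichotomous scale". Suicide attempts are in neither list. Separately, Ethics Approval states: "All serious adverse events will be monitored and reported to the Medical Ethical Committee".

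Study Design will "compare the outcomes of the BITT intervention group (n=50) with the outcomes of a WLCG (n=50", and gives the waitlist group BITT after the 3-month assessment (T2). Power Analyses covers only a standardised mean difference of 0.5.

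**The concern.** The objective and the analysis ask different questions. The objective is that attempts do not increase. The analysis tests whether the arms differ. When events are few, a test of difference will usually be non-significant whether or not treatment raises the risk, so that result carries little information about safety.

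The source of the outcome is also unclear. A 0-10 score for ideation or self-harm does not yield the yes/no attempt variable that the analysis names, and none of the listed yes/no topics is an attempt.

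At stake is what the trial may say about harm. The article's Introduction reports that 20.1% of adolescents with PTSD had attempted suicide, measured at age 18. A statement that BITT does not increase attempts would need an interval that excludes an increase of concern.

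**Working it through.** **The plan's own figure.** Power Analyses gives 66 evaluable participants and inflates for 25% dropout: 66 / 0.75 = 88, which reproduces. That calculation concerns a continuous outcome. No figure is given for attempts, so none can be reproduced.

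**Inputs.** 50 per arm (Study Design); 37 per arm after 25% dropout (50 × 0.75 = 37.5, rounded down). Two-sided alpha 0.05 is assumed, as the article states none. No attempt rate over three months is given, and the 20.1% at age 18 is not one, so control rates of 2%, 5%, 10% and 20% are assumed.

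**Step 1: power to detect a doubling.** Fisher power is the sum over all (i, j) of Bin(i; n, p0) × Bin(j; n, 2·p0), counting only tables with j > i and Fisher p < 0.05. The normal approximation is shown beside it, because a GEE Wald test may lie nearer to that. The last column is (1 − p0)^50.

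| Control → BITT | Fisher, 50/arm | Normal, 50/arm | Fisher, 37/arm | n/arm for 80% power (normal) | P(no control events), 50/arm |
|---|---|---|---|---|---|
| 2% → 4% | 0.6% | 8.4% | 0.2% | 1141 | 36.4% |
| 5% → 10% | 6.3% | 15.5% | 3.5% | 435 | 7.7% |
| 10% → 20% | 19.5% | 28.6% | 14.2% | 199 | 0.5% |
| 20% → 40% | 51.5% | 59.0% | 38.2% | 82 | 0.0% |

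For control rates of 2% to 10%, a true doubling would be missed with probability 80% to 99% by Fisher (100 − 19.5 and 100 − 0.6), or 71% to 92% by the normal formula. A tripling from 5% to 15% has Fisher power of 24.4%.

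**Step 2: what a reassuring result would exclude.**
- With 0 of 50 events, the exact two-sided 95% upper limit is 1 − 0.025^(1/50) = 7.1%. With 0 of 37 it is 9.5%.
- With equal counts in two arms of 50, the score-based (Newcombe) 95% interval for the risk difference reaches +7.1 points (0 vs 0), +8.7 (1 vs 1), +9.9 (2 vs 2) and +12.7 (5 vs 5).
- Six BITT attempts against one control attempt gives Fisher p = 0.11, with an interval from −0.6 to +21.9 points. The test is non-significant, yet the data are compatible with a large increase.

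**Step 3: estimability.** If one arm has no events, its log odds are unbounded and the logit contrast between arms has no finite estimate. With equal true rates, the chance that at least one arm is empty is 1 − (1 − q)², where q is the last column of the table: 1 − 0.636² = 0.60 at 2%, 1 − 0.923² = 0.15 at 5%, and 1 − 0.995² = 0.01 at 10%.

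**Step 4: time window.** After T2 both arms have had BITT or been offered it. Attempts at T3 and T4 therefore add nothing to the randomised comparison with no BITT. Repeated records up to T2 come from the same participants, so they do not enlarge the sample either.

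**The case against.** The strongest reply has four parts.

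- **Measurement.** The article describes 15 questionnaire items by topic, not by wording. A reader might infer that attempts go unrecorded. The document does not support that: an unlisted item may ask about them, and serious adverse event monitoring may capture them. This part stands, and what remains is a request to name the source. The monitoring paragraph does not name attempts or tie the reports to the GEE outcome, so the question is still open.

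- **Inference.** A reader might infer that the investigators will treat p > 0.05 as proof of safety. Nothing in the article says so. GEE can also give an estimate with an interval when both arms have events, so the model family is not itself the fault. A margin, or a rule for sparse events, could sit in an analysis plan that is not shown. That also stands. What the article does fix is a tested group difference set against a no-increase objective, and those two do not match.

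- **Size.** The rates are assumed, and the results depend on them: Fisher power for a doubling runs from 0.6% to 51.5%. Fisher is also more conservative than a Wald test. Both points are fair, but the normal approximation reaches only 59% at the highest assumed rate, so the conclusion holds across the range.

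- **Weight.** This is one component of one secondary objective. Self-harm, ideation and serious adverse events also inform safety, and any trial of 100 has little power for uncommon harms. No analysis creates that missing information. An interval shows how much is missing; a non-significant test does not.

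**Conclusion.** The point holds at moderate severity. The GEE difference test does not match the objective that BITT not increase suicide attempts, and a non-significant result could not support that objective. Under assumed control rates of 2% to 10% and 50 per arm, Fisher power to detect a doubling is about 1% to 20%, rising to about 52% at 20%. Zero events in 50 leaves increases up to about 7 points unexcluded. At low rates the planned contrast may have no finite estimate. These figures rest on the assumed rates, two-sided alpha 0.05, and a comparison of participants with any attempt up to T2 in place of the GEE itself.

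The missing source is a matter of clarification only. Nor does the point undermine the trial: the primary outcomes, the randomisation and the sample size for PTSD symptoms are unaffected.

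**What to change.** 1. Name the source of the attempt data: confirm which questionnaire item records attempts, or state that they come from the serious adverse event records, and confirm that those records hold attempts for both arms.
2. Replace or supplement the GEE for attempts with counts by arm from T0 to T2 and the risk difference with an exact or score 95% confidence interval, which remains available when an arm has no events.
3. Tabulate attempts in the waitlist group after it receives BITT separately, outside the randomised comparison.
4. Word the safety conclusion by the largest increase that the interval excludes, and state that p > 0.05 will not be taken as evidence of no increase.

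The cost is a change of analysis wording and an extract of safety data. No extra participants or visits are needed, and the article has data collection running until December 2025. The downside is a more modest safety claim.

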### Ethics Approval

This study will be conducted in accordance with the Declaration of Helsinki. The ethics review board of the Amsterdam University Medical Center in the Netherlands approved this study (2022.0347, September 12, 2022). We will handle participant data in compliance with the General Data Protection Regulation (GDPR). All adolescents will give written informed consent, and legal guardians of adolescents aged 12-15 years will also provide consent before conducting any study procedures. All serious adverse events will be monitored and reported to the Medical Ethical Committee of the Amsterdam University Medical Center until the end of the study. In addition, during the measurements (directly, 3, 6, and 9 months after the BITT) we assess PTSD symptoms, comorbid symptoms, and risk behavior. In case of safety concerns, we contact the referring professional of the adolescent. Participants will receive a voucher of 10 euros (US $11.36) upon completing the final measurement.

